# Clinical and Economic Evaluation of a Real-Time Chest X-Ray Computer-Aided Detection System for Misplaced Endotracheal and Nasogastric Tubes and Pneumothorax in Emergency and Critical Care Settings: Protocol for a Cluster Randomized Controlled Trial

**DOI:** 10.2196/72928

**Published:** 2025-08-20

**Keywords:** computer-aided detection system, artificial intelligence, pneumothorax diagnosis, endotracheal tube, nasogastric tube, clinical effectiveness, cost-effectiveness

## Abstract

**Background:**

Advancements in artificial intelligence (AI) have driven substantial breakthroughs in computer-aided detection (CAD) for chest x-ray (CXR) imaging. The National Taiwan University Hospital research team previously developed an AI-based emergency CXR system (Capstone project), which led to the creation of a CXR module. This CXR module has an established model supported by extensive research and is ready for application in clinical trials without requiring additional model training. This study will use 3 submodules of the system: detection of misplaced endotracheal tubes, detection of misplaced nasogastric tubes, and identification of pneumothorax.

**Objective:**

This study aims to apply a real-time CXR CAD system in emergency and critical care settings to evaluate its clinical and economic benefits without requiring additional CXR examinations or altering standard care and procedures. The study will evaluate the impact of CAD system on mortality reduction, postintubation complications, hospital stay duration, workload, and interpretation time, as wells as conduct a cost-effectiveness comparison with standard care.

**Methods:**

This study adopts a pilot trial and cluster randomized controlled trial design, with random assignment conducted at the ward level. In the intervention group, units are granted access to AI diagnostic results, while the control group continues standard care practices. Consent will be obtained from attending physicians, residents, and advanced practice nurses in each participating ward. Once consent is secured, these health care providers in the intervention group will be authorized to use the CAD system. Intervention units will have access to AI-generated interpretations, whereas control units will maintain routine medical procedures without access to the AI diagnostic outputs.

**Results:**

The study was funded in September 2024. Data collection is expected to last from January 2026 to December 2027.

**Conclusions:**

This study anticipates that the real-time CXR CAD system will automate the identification and detection of misplaced endotracheal and nasogastric tubes on CXRs, as well as assist clinicians in diagnosing pneumothorax. By reducing the workload of physicians, the system is expected to shorten the time required to detect tube misplacement and pneumothorax, decrease patient mortality and hospital stays, and ultimately lower health care costs.

**International Registered Report Identifier (IRRID):**

PRR1-10.2196/72928

## Introduction

### Background

Misplacement of medical tubes, such as endotracheal tube (ETT) and nasogastric tube (NGT), is a well-recognized clinical issue associated with serious complications, including pneumothorax, aspiration pneumonia, prolonged hospital stays, and even mortality [1-5]. Delayed management of pneumothorax could lead to tension pneumothorax, which is a life-threatening condition. In addition, misplacement of an ETT would cause hypoxia in critically ill patients. Misplacement of the NGT could lead to aspiration pneumonia. Taken together, these 3 conditions increase patient mortality, particularly related to respiratory causes. Portable chest radiography (chest x-ray [CXR]) is routinely performed in intensive care and emergency settings to confirm tube placement and detect complications. However, interpretation of portable CXR images can be challenging due to factors such as patient immobility and lower image quality, which may delay clinical decisions and increase the risk of adverse events. Therefore, with the rise of deep learning applications in the field of medical imaging, the development of artificial intelligence (AI) algorithms for CXRs has significantly enhanced the capabilities of image quality identification [6], and driving the development of computer-aided detection (CAD) systems for CXR imaging [7,8].

These systems support clinicians in diagnosing cardiopulmonary diseases, detecting pneumothorax, and preventing adverse events caused by improper tube placements. CXR imaging plays a vital role in assisting physicians with the diagnosis of cardiopulmonary conditions or pneumothorax and in identifying tube misplacements, as it is generally recommended to perform a CXR examination following the placement of ETT or NGT to confirm correct positioning [9,10]. Previous studies have demonstrated that deep learning models exhibit excellent performance in interpreting CXRs, particularly in detecting malpositioned tubes and thoracic abnormalities [11-15]. However, the development of these AI-CAD systems has typically relied on retrospective data and focused primarily on comparing their diagnostic accuracy with that of human clinicians. As a result, evidence remains limited regarding whether these AI-CAD systems can indeed deliver tangible clinical benefits when implemented in real-world clinical practice. Further validation through prospective studies, multicenter evaluations, and cost-effectiveness analyses is warranted to establish their real-world utility. Moreover, considering the increasing emphasis on health care sustainability and the need to allocate limited resources effectively, it is crucial to evaluate whether the adoption of AI-based CAD systems represents a worthwhile investment for health care systems.

In previous studies, we developed a real-time CAD system for emergency and critical care CXR imaging, incorporating deep learning technologies to detect mispositioned ETT and NGT as well as pneumothorax [16-18]. The system’s modules have demonstrated its potential to improve diagnostic efficiency, reduce adverse events related to tube misplacement, and enhance patient outcomes. However, its clinical efficacy and cost-effectiveness have yet to be validated through rigorous randomized clinical trial and economic evaluations. To bridge this gap, this project aims to conduct comprehensive clinical trials (prospective studies and multicenter evaluations) and cost-effectiveness assessments, thereby enhancing the system’s credibility and value for real-world clinical applications.

### Objective

This study aims to apply the AI-based CAD system for automatic detection and assessment of catheter placement and pneumothorax in emergency and intensive care settings. We aim to evaluate the clinical and economic benefits of the CAD system via rigorous randomized trial without altering routine care and procedures.

In terms of clinical benefits, the study will assess whether the use of the CAD system reduces mortality and will evaluate hospital stay duration, the time required to detect misplacement, and the time needed to reposition ETTs, NGTs, and chest drainage tubes. For the economic evaluation, the study will compare the cost-effectiveness of using the CAD system versus standard care without CAD.

### Prior Work

#### Overview

Our team selected a CXR module developed through the Capstone project (MOST 111-2634-F-002-015-, Capstone project) in collaboration with the commercial product provided by EBM Technologies, which has been approved by the ethics committee of National Taiwan University Hospital (NTUH; reference number: 202003106RINC). The CAD system automatically retrieves CXR images from the hospital’s Picture Archiving and Communication System, processes them within approximately 1 minute, and generates predictive results displayed on a centralized platform for clinical review. Alerts for abnormal findings are sent via text notifications to facilitate timely intervention. This system has been deployed in emergency and intensive care units (ICUs) to automate the identification and detection of mispositioned ETT and NGT on CXR images.

#### The Model of Localization and Detection of Malpositioned ETT

This model uses CXR images collected from NTUH, including both the Taipei main hospital and the Yunlin branch, which were divided into a training dataset and a testing dataset. The training dataset primarily consists of 5767 images collected from NTUH between 2015 and 2019. The testing dataset includes images from both chronological and geographical contexts: 955 images from NTUH during 2020 (NTUH-20 dataset) and 656 images from the NTUH Yunlin Branch (NTUH-YB dataset), representing different temporal and geographical backgrounds. During the image annotation process, the research team marked the position of the ETT and identified the instances of misplacement. The marking was done by nurse practitioners, emergency physicians, and radiologists with extensive clinical experience, and the images were classified according to whether the ETT was misplaced. The model uses a 2-stage model architecture for image processing.

The model uses a 2-stage architecture: DeepLabv3+ with ResNeSt50 as the backbone for segmenting the ETT, trachea, and main bronchi, followed by DenseNet121 for classifying ETT misplacement. Transfer learning was applied, using pretrained ImageNet weights fine-tuned on the dataset. The system demonstrated excellent performance. For segmentation, the Dice coefficients were 0.854 (NTUH-20 dataset) and 0.839 (NTUH-YB dataset), accurately delineating ETT contours. Mean tip localization errors were 1.107 cm (95% CI 0.807-1.513; NTUH-20) and 1.118 cm (95% CI 0.956-1.319; NTUH-YB). For classification, the system achieved area under the curve (AUC) scores of 1.000 (NTUH-20) and 0.994 (NTUH-YB) for ETT presence, and 0.847 (NTUH-20) and 0.734 (NTUH-YB) for ETT misplacement. It excelled in detecting one-lung intubation, with AUC of 0.991 (NTUH-20) and 0.966 (NTUH-YB), highlighting its robustness in critical scenarios. Results are summarized in Figure 1.

**Figure 1 figure1:**
[figure not shown]
Summary of the model of localization and detection of malpositioned endotracheal tube (ETT). (A) original chest x-ray images. (B) Pixel-level annotations used by the labelers, including the ETT (brown) and the trachea and main bronchi (red), with dark brown dots indicating the ETT tip. (C) Segmentation masks generated by the segmentation model. (D) The gradient-weighted class activation mapping (Grad-CAM) results, highlighting that the classification model primarily relied on the region surrounding the ETT tip for its inferences.

#### The Model for Misplacement Detection of NGTs

A total of 7378 portable CXRs were collected from NTUH Taipei main hospital and Yunlin branch (2015 to 2020) and annotated for NGT localization and malposition. The CAD system used DeepLabv3+ (ResNeSt50 backbone) for segmentation and DenseNet121 for classification. Testing on NTUH-20, NTUH-YB, and CLiP datasets demonstrated strong performance.

The segmentation model achieved Dice coefficients of 0.665 (NTUH-20) and 0.646 (NTUH-YB), with mean NGT tip localization errors of 1.64 cm and 2.83 cm, respectively. The classification model demonstrated strong performance, with an AUC of 0.998 for NGT detection and 0.964 (NTUH-20) and 0.991 (NTUH-YB) for malposition detection.

In summary, this deep learning–based model for tube misplacement detection demonstrated excellent performance in detecting and localizing ETT and NGT. Its accuracy and reliability highlight its potential for broad applications in emergency and intensive care settings.

#### The Model for Pneumothorax Detection

A deep learning–based dual-model system was developed for diagnosing and localizing pneumothorax on portable supine CXRs in emergency and intensive care settings. Images from NTUH (Taipei main hospital and Yunlin branch), collected between 2015 and 2020, were divided into training (1571 images) and test (1071 images) datasets, with pixel-level annotations.

The detection system used EfficientNet-B2, DenseNet-121, and Inception-v3 for classification, and Deformable DETR, TOOD, and VFNet for localization. The segmentation system used UNet for both classification and localization. The detection system achieved an AUC of 0.940, and the segmentation system achieved an AUC of 0.979, both performing similarly to radiology reports. The detection system achieved a Dice coefficient of 0.758, and the segmentation system achieved a Dice coefficient of 0.681, showing high accuracy.

These systems demonstrate strong performance and generalizability, offering potential to assist health care facilities in prioritizing critical x-rays and notifying clinicians for timely interventions, improving patient outcomes. Results are summarized in Figure 2.

**Figure 2 figure2:**
[figure not shown]
Summary of the model for pneumothorax detection. (A) Original image. (B) Boundary boxes (green rectangles) and segmentation masks (red regions) after preprocessing by the detection and segmentation model systems. (C) Boundary boxes (red rectangles) predicted by the detection model system. (D) Segmentation masks (purple regions) predicted by the segmentation model system.

The AI-based computer-aided diagnostic system automatically detects and assesses catheter placement and pneumothorax, providing excellent prejudgment capabilities for potentially misplaced catheter images. It reduces delays between obtaining CXR images and clinical interpretation, thus improving clinician efficiency. This, in turn, helps to reduce adverse reactions from catheter misplacement and subsequent management of pneumothorax, thereby improving patient prognosis and reducing complications.

This study focuses on the clinical validation and deployment of this system rather than on algorithm development or segmentation metrics. Although several foundational studies involving segmentation performance and metrics such as the Dice coefficient were conducted within the NTUH health care system, this trial aims to extend the findings and tools developed in those earlier studies to a broader range of health care settings. To enhance the generalizability and applicability of the research across institutions with varying levels and organizational structures, we have included 3 participating sites: a medical center (NTUH), and 2 regional hospitals (Fu Jen Catholic University Hospital [FJCUH] and Min-Sheng General Hospital [MSGH]).

## Methods

### Research Design

This study adopts a 2-phase design, beginning with a pilot study followed by a multicenter cluster randomized clinical trial. The pilot phase focuses on integrating a CXR CAD system into the hospital’s medical information systems, ensuring smooth functionality within the clinical workflow. The system will undergo testing and initial evaluations in the emergency intensive care and ICU at NTUH over a period of 6 to 12 months.

Building on the pilot phase, the multicenter clinical trial involves ICUs from NTUH, FJCUH, and MSGH. A total of 18 ICU units will participate, with NTUH contributing 14 units and the remaining hospitals contributing 2 units each. These units will be randomized into AI-assisted and control groups. Stratification is based on ventilator use, with randomization conducted within each stratum using uniform distribution. The AI-assisted group allows physicians to access real-time predictions from the CAD system during patient care. These predictions, generated within seconds, focus on identifying critical conditions, such as NGT misplacement, ETT misplacement, and pneumothorax. However, physicians in the control group will adhere to standard procedures without viewing AI-generated predictions, though the CAD system will still analyze images for internal validation. To minimize potential bias, both the outcome assessors and data analysts will remain blinded to group allocation throughout the data collection and statistical analysis phases.

The primary outcome is patient all-cause mortality rate: Assess whether the in-hospital mortality rate decreases after the intervention, reflecting the AI-assisted detection system’s ability to identify life-threatening conditions in a timely manner and facilitate rapid clinical intervention.

The secondary outcomes are as follows:

Cause-specific mortality rate: a physician panel, blinded to group allocation, will adjudicate the cause of death among study participants. The focus will be placed on respiratory-related mortality, which is most relevant to the conditions targeted by the AI modules.Length of hospital stay: evaluate whether the use of the AI-assisted system shortens hospitalization duration, particularly by enabling earlier detection of tube misplacement and pneumothorax, leading to timely treatment.Time to misplacement detection: determine whether the AI system reduces the time required to identify misplaced tubes or pneumothorax, thereby enhancing the timeliness of clinical interventions.Time to reposition ETT and NGT, and time to place a chest drain for pneumothorax.Direct medical costs (eg, x-ray examinations, intubation fees, and hospitalization costs) and indirect medical costs (eg, CAD system costs and labor costs).

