#### Phase 2: Cluster Randomized Controlled Trial

Building on the results of phase 1, this phase will expand to include the ICUs of FJCUH and MSGH, conducting a cluster randomized controlled trial from January 1, 2026, to December 31, 2027, to evaluate the practical application of the CAD system in a multicenter setting, as well as to assess clinical and economic benefits. In addition, the attending physicians, residents, and specialized nurses in the ECC and ICUs will sign consent forms, which will allow them to use the CAD system. Patients will be exempted from providing informed consent, as the study poses minimal risk, and the potential risks for participants are no greater than those for nonparticipants. Exempting informed consent will not affect their rights. The inclusion and exclusion criteria are shown in Textbox 2.

The study will use cluster randomization, stratified by ventilator use frequency, to balance the risk of pneumothorax between the 2 groups and reduce potential confounding bias. Within each stratum, the ventilator use will be similar, while the difference in use between strata will be larger. A uniform distribution will be applied to assign each ward unit a random probability. On the basis of these probabilities, the units will be ranked and assigned to either the intervention or control group based on their odd or even rank.

In the control group, physicians will continue with the current diagnostic process and will not be able to view the model’s predictions. In the intervention group, physicians will be authorized to access the AI model’s predictions during patient care as an additional decision-making reference. These predictions will be generated in seconds and can help identify issues such as tube misplacement (eg, NGT and ETT) and pneumothorax through AI analysis of CXRs, which will alert the physician to review the images. Access to the model’s prediction interface was restricted to physicians in the intervention group, with access for the control group technically disabled through role-based permissions within the hospital information system. This measure ensured that physicians in the control group were not exposed to any AI-generated outputs. In addition, to promote consistent use of the CAD system within the intervention group, log-in records will be monitored, and reminders will be issued in cases of noncompliance.

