Data collection included the total number of patients in the ward, the number of patients using ventilators, the number of pneumothorax cases, CXR results, misplacement detection time, mortality rate, length of stay, ETT resetting time, NGT resetting time, pneumothorax drainage tube placement time, direct medical costs (eg, x-ray examinations, intubation fees, and hospitalization fees), and indirect medical costs (eg, CAD system costs and labor costs). The implementation costs are expected to differ between the intervention and control arms. The intervention arm includes additional expenditures related to AI system deployment, such as system infrastructure, routine maintenance, training, and IT support. These costs are captured as part of the economic evaluation to assess whether the clinical benefits of AI-assisted care justify the associated investment. Imaging data will not be collected, and the AI software will not undergo model training.

The inclusion and exclusion criteria for cluster randomized controlled trial.

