### Statistical and Cost-Effectiveness Analysis

Statistical analysis will be conducted using SAS software (SAS Institute) to evaluate the outcomes of this study. Continuous variables, such as clinical outcomes and procedural times, will be summarized using descriptive statistics, including the number of observations, mean, median, SD, range, and 95% CIs. For categorical variables, frequency counts and percentages will be used to summarize the data.

In terms of clinical effectiveness, the primary outcome will be in-hospital mortality, and a proportional test will be used to compare the mortality rates between ICUs that have implemented the AI-assisted detection system and those that have not. The secondary clinical outcomes, which include the length of stay in the hospital, time to detect tube misplacements, and the time taken for medical interventions (such as repositioning of ETT and NGT and placement of pneumothorax drainage), will be analyzed using *t* tests for continuous variables. For categorical outcomes, including the rates of misplacement and other related interventions, chi-square test will be used. In addition, proportional tests will be conducted to examine the differences in the frequency of interventions across the 2 groups.

The study will also incorporate a health care technology and economic evaluation framework to assess the cost-effectiveness of the AI system alongside its clinical effectiveness. This evaluation will explore whether the clinical benefits derived from the AI system justify the associated resource consumption. Previous research by the team [21], such as the use of Markov models in gastric cancer screening and prevention, has demonstrated the utility of such economic evaluations, particularly in quantifying the cost-effectiveness of medical interventions and their impact on mortality reduction.

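### Mortality is to be compared by an unadjusted test, and the phase 2 data list names no patient-level prognostic variable, so a case-mix difference between the 18 units would be read as a CAD effect

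*Protocol article*

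**What the plan says.** All references are to the Methods of the protocol article.

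- **Clusters (Research Design).** "A total of 18 ICU units will participate, with NTUH contributing 14 units and the remaining hospitals contributing 2 units each". Units are ranked on a random number within strata and go to an arm by odd or even rank, which gives about 9 per arm. One hospital's 14 units will therefore almost certainly fall in both arms.
- **Stratification (Phase 2).** Randomisation is "stratified by ventilator use frequency, to balance the risk of pneumothorax between the 2 groups and reduce potential confounding bias". This is the only design factor, and it describes units, not patients.
- **Blinding (Research Design).** "both the outcome assessors and data analysts will remain blinded to group allocation throughout the data collection and statistical analysis phases". Unit staff are not included and could not be. They consent to use the system, control-arm access is disabled, and in the intervention arm "log-in records will be monitored, and reminders will be issued in cases of noncompliance".
- **Patient entry (Phase 2).** Adults qualify during 2026-2027 when a chest x-ray is needed for a tube or ventilator. "Patients will be exempted from providing informed consent".
- **Data (Phase 2).** "Data collection included the total number of patients in the ward, the number of patients using ventilators, the number of pneumothorax cases, CXR results", followed by process times, mortality, length of stay and costs. No age, admission type, diagnosis or severity item is named.
- **Primary analysis (Statistical and Cost-Effectiveness Analysis).** "a proportional test will be used to compare the mortality rates between ICUs" with and without the system. No covariate, stratum or unit term is given.

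**The concern.** Randomising units makes the units comparable in expectation at the time of allocation. It does not settle which patients each unit receives over the next two years. Two routes lead to different case mix in the two arms. One is chance: 18 units are few, ICUs can differ widely in the patients they take, and ventilator use is one coarse stratifier. The other is placement after allocation, which is possible where one hospital has units in both arms and the staff know which is which.

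The stated safeguards do not correct either route. Blinded assessors add little when the outcome is all-cause death. The stratifier reflects unit-level ventilator use, not who is admitted during the trial. The consent waiver removes selection through consent, which is a real strength, but not selection through placement.

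The target effect is 3 percentage points (28% to 25%). ICU mortality depends strongly on who is admitted, so a modest case-mix difference could hide part of an effect of that size or imitate it.

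**Working it through.** **Inputs from the article.** Mortality 28% and 25%; ICC 0.01; one-sided 5%; 5450 patients per arm; 18 units, taken as 9 per arm.

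**The plan's own figure.** 28% v 25% with 80% power, one-sided 5%, needs 2675 per arm without clustering. The stated 5450 implies a design effect of 5450/2675 = 2.04, that is, about 105 patients per unit. With 9 units per arm there are 5450/9 = 606 per unit, and the design effect is 1 + 605 × 0.01 ≈ 7.05. So 5450 does not follow from 18 units. That is a separate matter; 5450 is used here only to set the unit size.

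**Cluster standard error.**
SE = sqrt{ [p1(1−p1) + p2(1−p2)] × [ICC + (1−ICC)/m] / 9 }
= sqrt{ (0.2016 + 0.1875) × (0.01 + 0.99/605.6) / 9 }
= sqrt{ 0.3891 × 0.011635 / 9 } = 0.0224, or 2.24 points.

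This SE allows for clustering, so the figures below isolate case mix from the missing cluster term. A plain two-sample test would use sqrt(2 × 0.28 × 0.72/5450) = 0.86 points and would call 1.645 × 0.86 = 1.4 points significant.

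**Size of a shift (assumed values).** Suppose a fraction s of each arm is exchanged, so that patients with mortality p_high are in one arm in place of patients with mortality p_low. The contrast moves by 2 × s × (p_high − p_low).

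| s | p_high v p_low | shift |
|---|---|---|
| 2% | 40% v 25% | 0.6 points |
| 5% | 40% v 25% | 1.5 points |
| 2% | 45% v 20% | 1.0 point |
| 5% | 45% v 20% | 2.5 points |

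Neither the fractions nor the mortalities come from the article.

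**Effect on the test.** With no true CAD effect, the chance of a one-sided claim of benefit is P(T > 1.746), where T is noncentral t with 16 degrees of freedom and noncentrality ± shift/2.24. Direction matters.

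| shift | sicker patients in control units | sicker patients in CAD units |
|---|---|---|
| 0.6 | 8.2% | 2.9% |
| 1.0 | 11.2% | 1.9% |
| 1.5 | 15.8% | 1.1% |
| 2.5 | 28.2% | 0.3% |

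In the last column the harm is lost power. With a true 3-point effect the noncentrality is (3 − shift)/2.24. Power falls from about 36% with no shift to about 27% at 0.6 points and 8% at 2.5 points.

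These are rates given a shift of that size. A correct cluster SE already allows, on average, for chance differences between units. It does not allow for systematic placement, and it does not remove a chance imbalance from the estimate of the one trial that is run.

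**Gain in precision from adjustment (assumed values).** If the covariates explain 25% to 50% of the between-unit and 20% of the within-unit variance, the bracket becomes 0.0075 + 0.8 × 0.99/605.6 = 0.00881, or 0.0050 + 0.00131 = 0.00631. The SE falls to 1.95 or 1.65 points.

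**The case against.** **The data list is not complete.** The article elsewhere commits to adjudicated cause of death, quality-adjusted life years and log-in records, none of which is in the list. Baseline variables are often left to the full protocol. This stands: it cannot be concluded that severity will not be collected. But the article does more than stay silent. It names the primary test, and that test is unadjusted.

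**Steering is not documented.** A reader might infer that sicker patients will be sent to, or away from, CAD units by staff who know the allocation. The article does not support that. It does not say who assigns beds, whether they know the arm, or whether the 14 units take interchangeable patients. It also gives them no stated reason to act on a reading aid. This stands, and the point does not need steering, since chance imbalance among 18 units is enough to justify adjustment.

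**A shift would not be invisible.** A reader might also infer that the analysts could not see a change in case mix. That goes too far. Ventilator and pneumothorax counts are collected during the trial and would give a crude signal by arm. They would not permit patient-level adjustment.

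**Error inflation runs one way only.** The rise to 8% to 28% applies only if sicker patients are in control units. The reverse makes the test conservative and costs power.

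**The primary outcome may change.** The Determination of Sample Size section allows a switch after the pilot, for example to time to detection. The mortality consequence is therefore conditional, but mortality is the outcome and test now stated.

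**Conclusion.** The concern holds in a limited form. The article fixes an unadjusted comparison of mortality in a design with 18 clusters, patient entry after allocation, unblinded unit staff and one unit-level stratifier, and its data list names nothing at patient level with which to adjust. A case-mix difference, however it arises, would be read as a CAD effect. Under the assumed shifts of 0.6 to 2.5 points, the false-positive rate is about 8% to 28% if the shift favours CAD, and about 3% to 0.3%, with reduced power, if it goes against CAD. These figures rest on assumed exchange fractions and mortalities, 9 equal units per arm and the article's ICC of 0.01. They show how sensitive the result is; they do not predict a bias. The change should be made, but nothing shows that the arms will in fact differ.

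**What to change.** 1. **Data.** In the phase 2 list, add for each eligible patient, at first entry to a trial unit and from existing records: age, admission type, ventilation status and the severity score already recorded, if there is one.
2. **Analysis.** In Statistical and Cost-Effectiveness Analysis, replace the plain proportional test for mortality by a mixed model with a unit effect, the ventilator stratum and these baseline values. A two-stage analysis of risk-adjusted unit rates would also serve. Either needs a small-sample correction for 18 clusters. Use only values that precede or coincide with entry, so that nothing affected by CAD is adjusted away.
3. **Reporting.** Show these values by arm and by unit, so that a reader can judge case mix directly.

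If the full protocol already lists such variables, only the analysis sentence and the reporting need to change. The cost is extraction work and a stated rule for missing values, some of which are to be expected. No extra patients, visits or x-rays are needed, and care does not change.
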